### Sample size

The primary outcome is unplanned hospitalisation (inpatient admissions) in the 12 months following pulmonary rehabilitation. In our published Phase II trial,^23^ 57% of the centre-based group were free from hospitalisation at 12 months, whereas 78% of rehabilitation completers were free from hospitalisation (regardless of group). Completion was 91% for HomeBase, and 49% for centre based.^23^ The novel aspect of the current study is that intervention participants will be offered a choice of models. Based on our experience recruiting for HomeBase, we expect that 75% of individuals may select a home programme of whom 91% will complete, and 25% will select centre-based of whom 49% will complete. We thus anticipate a completion rate of 80% in the intervention (choice) group.

At 80% completion, our data indicate that 72% of the intervention group would remain free from admission at 12 months, compared with the observed rate of 57% in centre-based (control) participants.^23^ We thus expect 15% reduction in hospitalisations in the intervention group (choice of home-based or centre-based rehabilitation) compared with control (centre-based rehabilitation only). To detect a difference in remaining free from hospitalisation between intervention and control groups of 15% (72% vs 57%) with 80% power and a two-sided 0.05 significance level, 312 participants (156 in each group) are required. Adjusting for clustering by programme (intracluster correlation coefficient of 0.01, based on our published two-site trial and 35 participants per cluster), the total required sample is 418. Our previous study had 10% loss to follow-up, so to allow for this we will recruit a total of 490 participants from 14 pulmonary rehabilitation programmes.

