A low-cost model of delivering pulmonary rehabilitation directly into the home was developed (HomeBase) in Australia to improve access and uptake.^22^ A previous Phase II randomised controlled equivalence trial^23^ showed that HomeBase delivered equivalent clinical outcomes (exercise capacity, symptoms and quality of life) to traditional centre-based rehabilitation in COPD with similar costs and better completion rates (91% vs 49%). The clinical implementation of home-based pulmonary rehabilitation programmes has the potential to improve health outcomes, reduce healthcare utilisation and minimise societal costs but should not be considered a replacement for traditional centre-based programmes. Semi-structured interviews with participants who received home-based rehabilitation in the Phase II trial revealed that participants valued the convenience and flexibility of exercise training at home, and the reduced travel burden of a home-based programme.^24^ However, 18% of individuals assessed for eligibility to that trial declined to participate because they wanted to be certain they would receive their preferred choice of a traditional centre-based programme.^23^

A recent ATS workshop report identified that the emergence of alternative models of pulmonary rehabilitation pose many unanswered questions for clinical practice, which will be best addressed by prospective clinical implementation trials.^8^ At a health service or programme level it is likely that the best outcomes and optimal completion rates will be achieved by offering patients a choice of pulmonary rehabilitation locations. Our previous equivalence trial of home versus centre-based rehabilitation showed that patients who completed pulmonary rehabilitation, regardless of group allocation, were 56% less likely to be hospitalised in the following 12 months and had a longer time to their next hospital admission.^23^ Offering the choice of home or centre-based pulmonary rehabilitation may increase programme completion and therefore result in fewer hospitalisations and more patients with COPD achieving improvements in exercise capacity, breathlessness and quality of life. Until now, the offer of choice of pulmonary rehabilitation location versus traditional centre-based only has not been investigated in a clinical trial.

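### The 72% admission-free rate planned for the choice arm does not follow from the completion argument given for it; the printed figures lead to about 70%, a 13-point rather than a 15-point effect

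*Protocol article*

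**What the plan says.** The Sample size section takes its inputs from the Phase II trial. For admission-free rates it reports "57% of the centre-based group were free from hospitalisation at 12 months, whereas 78% of rehabilitation completers were free from hospitalisation (regardless of group"). For completion it reports "Completion was 91% for HomeBase, and 49% for centre based".

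For the choice arm, "we expect that 75% of individuals may select a home programme of whom 91% will complete". The remaining 25% are expected to choose the centre, with 49% completing. The section puts overall completion at 80%.

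The planning rate follows directly: "At 80% completion, our data indicate that 72% of the intervention group would remain free from admission at 12 months". The section sets 72% against 57%, calls the 15-point gap the expected effect, and derives 312 participants without clustering, 418 with clustering, and a recruitment target of 490 from 14 programmes.

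The section states neither the admission-free rate of non-completers nor the rate in the Phase II home-based group. The Introduction gives the same causal argument: choice raises completion, and completion lowers hospitalisation.

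**The concern.** The 72% is presented as a consequence of 80% completion, so it should be recoverable from the completion rates and the completer rate printed beside it. It is not. With completers at 78%, the control figure and the choice-arm figure require different rates among non-completers.

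The 15-point difference drives every later number in the section. If the evidence cited supports a smaller effect, the chance of missing that effect is larger than a reader would take from the 80%. A non-significant result, judged against an expected 15 points, could then be misread as evidence that offering choice does not work.

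**Working it through.** **Inputs** (all from Sample size): completers 78% admission-free; centre-based group 57% admission-free with 49% completion; home completion 91%; 75% choose home and 25% centre; ICC 0.01; 35 per cluster; 10% loss; 490 recruited; two-sided 0.05.

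**1. Reproduce the plan.**
- Completion in the choice arm: 0.75 × 0.91 + 0.25 × 0.49 = 0.805, stated as 80%.
- Per arm for 72% v 57%, normal approximation with unpooled variance: (1.960 + 0.842)² × (0.72 × 0.28 + 0.57 × 0.43) / 0.15² = 155.8, so 156 per arm and 312 in total.
- Design effect: 1 + 34 × 0.01 = 1.34, and 312 × 1.34 = 418.
- Allowing for loss: 418 / 0.9 = 465, which the target of 490 exceeds.

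The sample-size arithmetic is right for 72% v 57%.

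**2. Non-completer rate implied by the control figure.** Write the admission-free rate as c × 0.78 + (1 − c) × q, where c is completion and q is the rate in non-completers.
- Control: 0.57 = 0.49 × 0.78 + 0.51 × q, so q = (0.57 − 0.3822) / 0.51 = 0.368.

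**3. Choice arm with the same q.**
- At 80%: 0.80 × 0.78 + 0.20 × 0.368 = 0.698.
- At 80.5%: 0.805 × 0.78 + 0.195 × 0.368 = 0.700.
- Effect: 12.8 to 13.0 points.

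**4. What 72% would require.** q = (0.72 − 0.80 × 0.78) / 0.20 = 0.48, against 0.368 from the control arm. With 78% in both models, no single q gives both figures.

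**5. Rounding.** Varying 57%, 78% and 49% by half a point each way, and choice-arm completion from 79.5% to 81%, gives effects from 11.9 to 13.9 points. None reaches 15.

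**6. Power.** Evaluable: 490 × 0.9 = 441, or 31.5 per cluster. Design effect: 1 + 30.5 × 0.01 = 1.305. Effective size per arm: 441 / 1.305 / 2 = 169.
- 72% v 57%: power 83%.
- 70% v 57%: standard error = √[(0.70 × 0.30 + 0.57 × 0.43) / 169] = 0.0519; 0.13 / 0.0519 − 1.960 = 0.545; power 71%.
- 69.8% v 57%: power 69%.
- With the plan's 1.34 instead of 1.305, the last two become 70% and 68%.

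**7. Evaluable participants for 80% power, by the plan's formula.**
- 70% v 57%: 212 per arm; 2 × 212 × 1.34 = 568.
- 69.8% v 57%: 219 per arm; 2 × 219 × 1.34 = 587.

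Both compare with the stated 418.

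**The case against.** The strongest reply is that 78% is a pooled figure, and the protocol does not say that it held separately in each model. If home completers did better than centre completers, the printed figures can be reconciled. Assume equal Phase II arms (the sizes are not given), non-completers 41% admission-free, centre completers 73.7% and home completers 80.3%:
- Pooled completers: (0.49 × 73.7 + 0.91 × 80.3) / 1.40 = 78%.
- Control: 0.49 × 0.737 + 0.51 × 0.41 = 57%.
- Choice arm: 0.6825 × 0.803 + 0.1225 × 0.737 + 0.195 × 0.41 = about 72%. The weights are 0.75 × 0.91, 0.25 × 0.49 and the remainder.

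This stands, so 72% and 57% are not impossible together, and the authors hold data that the reader does not. But the reconciliation needs home participants to do better than centre participants at the same completion status. The protocol neither reports nor argues such an advantage; it argues through completion alone.

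It is also fair to say that a sponsor may choose a target difference, and that the power statement is correct for 15 points. Both are accepted. The section, however, presents the 15 points as what its data lead it to expect, not as a chosen target.

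A reader might go further and use the Introduction's statement that completers "were 56% less likely to be hospitalised in the following 12 months" as a risk ratio. Non-completers would then be 1 − 0.22 / 0.44 = 50% admission-free, the choice arm 0.80 × 0.78 + 0.20 × 0.50 = 72.4%, and control 0.49 × 0.78 + 0.51 × 0.50 = 63.7%, an effect of about 9 points. The document does not support this. It does not say what measure the 56% is or whether it is adjusted, and the result displaces the observed 57%. Nor does it show that the authors obtained 72% this way, since the pooled reconciliation above is another route.

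**Conclusion.** Wrong as written, of moderate importance. On the completion argument the protocol gives, the choice arm should be about 70% admission-free and the expected effect about 13 points. Power for that effect is about 70% by the plan's own normal approximation, so the chance of missing it is about 30% rather than at most 20%.

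This rests on three assumptions: the 78% applies to completers of both models, non-completers share one rate, and the ICC and loss to follow-up are as planned. A home-specific advantage could restore 72%, but the document does not state one.

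A reader might infer that the sample size was miscalculated or that the 80% power claim is false. Neither follows: the 312, the 418 and the 80% are right for a 15-point difference. The fault is in how that difference is justified.

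**What to change.** In the Sample size section, and wherever the analysis plan repeats it:
- Derive both arms from the same completer and non-completer rates and change 72% to about 70%. Alternatively, keep 72% and state the Phase II home-specific rate that supports it. In the equal-arms example above, the home-based group would be 0.91 × 0.803 + 0.09 × 0.41 = about 77% admission-free.
- Describe 15 points as the difference the trial is sized to detect with 80% power, not as what the Phase II data indicate.
- Report power at about 13 points (about 70%) next to it, and refer to that figure when interpreting a null result.

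The cost is a few sentences and a less favourable stated power for the expected effect. No extra participants and no change in design or recruitment are needed. The article reports recruitment as ongoing, so the correction can be made before results are interpreted.

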## Methods and analysis

### Design

A two-arm cluster randomised, controlled, assessor-blinded trial will be conducted with 14 centre-based pulmonary rehabilitation services across Australia. The overall trial design is depicted in figure 1. This trial protocol is reported in accordance with Standard Protocol Items: Recommendations for Interventional Trials guidelines.^25^ The trial has been prospectively registered at ClinicalTrials.gov, will be conducted in accordance with the principles of Good Clinical Practice and will be reported according to Consolidated Standards of Reporting Trials^26^ and Standards for reporting implementation studies (StaRI)^27^ standards for cluster randomised controlled trials and implementation studies.

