### Statistical analysis

Generalised linear mixed models will be used to analyse the primary outcome of hospitalisation, and linear mixed models will be used for continuous outcomes. These will account for correlation between participants within a cluster. Analyses will be based on intention-to-treat and the level of significance will be set at p< 0.05.

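### The stated 80% power makes no allowance for only 14 randomised services; on about 12 degrees of freedom it is about 76% at the 441 participants expected to be analysed

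*Protocol article*

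**What the plan says.** The Design section states that the trial "will be conducted with 14 centre-based pulmonary rehabilitation services across Australia", and the Randomisation section allocates those services 1:1, stratified by hospital or non-hospital setting.

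The Sample size section builds the target in three steps.

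- From the earlier trial it takes that "57% of the centre-based group were free from hospitalisation at 12 months", and it projects that "72% of the intervention group would remain free from admission at 12 months". The aim is put as "To detect a difference in remaining free from hospitalisation between intervention and control groups of 15% (72% vs 57%) with 80% power", and the section states that "with 80% power and a two-sided 0.05 significance level, 312 participants (156 in each group) are required".
- It then adjusts for clustering with an "intracluster correlation coefficient of 0.01, based on our published two-site trial and 35 participants per cluster", after which "the total required sample is 418".
- It allows for 10% loss to follow-up and recruits 490 from the 14 programmes.

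The Statistical analysis section says that "Generalised linear mixed models will be used to analyse the primary outcome of hospitalisation", that the models account for correlation within a cluster, and that significance is set at p<0.05. It names no test statistic, reference distribution or degrees of freedom.

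**The concern.** A design effect inflates the variance for correlation within services, but it leaves the critical value at 1.96. That is adequate with many clusters. Here treatment is assigned to 14 services, so the variance of the treatment contrast has to be judged from between-service variation with about 14 - 2 = 12 degrees of freedom, or 11 if the stratum is in the model. The critical value is then about 2.18 or 2.20, and power falls. The arithmetic in the article would give 418 whether there were 14 services or 140.

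This is the primary outcome and the comparison for which the trial is sized. If the test is valid for 14 clusters, the trial has less power than stated even when every planning assumption is right. If the test ignores the small number of clusters, its type I error exceeds the stated 0.05.

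**Working it through.** **Inputs from the Sample size section:** 57% and 72% free from hospitalisation; two-sided 0.05; 80% power; intracluster correlation (ICC) 0.01; 35 per cluster; 10% loss; 490 recruited from 14 services. **Assumptions added here:** seven services per arm and equal cluster sizes.

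**1. Reproducing the article's figures**

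- Variance term: 0.57 × 0.43 + 0.72 × 0.28 = 0.4467.
- Per arm: (1.960 + 0.842)² × 0.4467 / 0.15² = 155.8, so 156 per arm and 312 in total.
- Design effect: 1 + (35 - 1) × 0.01 = 1.34, and 312 × 1.34 = 418.
- Loss: 418 / 0.9 = 465 (rounded up). The planned 490 = 14 × 35 exceeds this. Expected analysed: 490 × 0.9 = 441, or 31.5 per service.

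Both 312 and 418 reproduce exactly, so the 80% is a large-sample figure.

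**2. Changing only the reference distribution**

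With N analysed and m per service, SE = sqrt(0.4467 / (N/2) × [1 + (m - 1) × 0.01]) and the non-centrality is 0.15 / SE. Power is then taken from the normal distribution (critical value 1.96) or from the non-central t on 12 degrees of freedom (critical value 2.179).

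| N analysed | m | Design effect | SE | 0.15/SE | Power, z | Power, t on 12 df |
|---|---|---|---|---|---|---|
| 418 | 35 | 1.340 | 0.0535 | 2.80 | 80.0% | 73.0% |
| 418 | 29.9 | 1.289 | 0.0525 | 2.86 | 81.5% | 74.7% |
| 441 | 31.5 | 1.305 | 0.0514 | 2.92 | 83.1% | 76.4% |
| 490 | 35 | 1.340 | 0.0494 | 3.03 | 85.9% | 79.5% |

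On 11 degrees of freedom the figure at 441 is 75.7%. With a pooled variance and 12 degrees of freedom it is 75.3%. Reaching 80% on 12 degrees of freedom with 14 services needs about 498 analysed, or about 554 recruited at 10% loss (498 / 0.9 = 553.3).

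**3. Sensitivity to the ICC** (values outside the article, for range only). At 441 analysed on 12 degrees of freedom, power is 81.3% at ICC 0.005 and 67.5% at ICC 0.02.

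**4. Simulation check.** Beta-binomial data, seven versus seven services, a random-intercept logistic model, 3,000 runs per setting.

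- Power at ICC 0.01 with 30 and 32 per service: 75.5% and 79.1% for the mixed-model Wald statistic referred to t on 12 degrees of freedom; 73.6% and 77.5% for a t test on service proportions. These are consistent with the analytic figure of about 76%.
- Type I error with 30 per service (Monte Carlo standard error about 0.4-0.5 points):

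| ICC | Wald z | Same statistic, t on 12 df | t test on service proportions |
|---|---|---|---|
| 0.01 | 6.3-6.6% | 3.7-3.8% | 4.7-5.1% |
| 0.02 | 7.6% | 5.1-5.2% | 4.9-5.3% |
| 0.05 | 9.4-9.9% | 6.3-7.0% | 5.1-5.7% |

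The ranges cover two null rates, 57% and 64.5% free from hospitalisation.

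**The case against.** A reader might infer that the planned mixed-model test itself treats 14 services as a large sample, and so that the trial's false-positive rate is already inflated. The article does not support that. It names a model class and a significance level, but no statistic, software or degrees of freedom, so there is no default to attribute to it. Such detail is commonly left to the statistical analysis plan, which is not shown and may well specify a small-sample method. Even if a Wald z test were used, the simulated error at the planned ICC is only about 6-7%; the larger figures need ICCs that the article does not use.

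The power gap is also small. Recruiting 490 where 465 would cover the loss recovers part of it, and power is within a point of 80% if nobody is lost. Loss on the primary outcome could be below 10%, because monthly calls are backed by medical record audit, although the article does not quantify this. The simulated mixed-model power of 75.5-79.1% suggests a shortfall of roughly 1-4 points, and t on 12 degrees of freedom is somewhat conservative at ICC 0.01. A halved ICC would remove the gap.

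These points limit the size and grade of the finding. They do not rescue the printed statement. The article ties 80% to 418, where a test on 12 degrees of freedom has 73-75%, and uncertainty in the ICC cuts both ways. The ICC of 0.01 comes from a two-site trial, which can say little about variation between services.

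**Conclusion.** The power statement is wrong as written: 80% at two-sided 0.05 is a large-sample figure that 14 randomised services do not deliver. On the article's own inputs, power is about 76% at the 441 expected to be analysed, 73-75% at the stated 418, and 79.5% with no loss. The gap at planned recruitment is about 4 points, so this is a correction to make and not a threat to the trial. The figures rest on ICC 0.01, a 7:7 split, equal cluster sizes and about 12 degrees of freedom. Unequal cluster sizes would lower power further.

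The type I error point is conditional. It applies only if a Wald z reference is used, and the article does not say so.

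**What to change.** - Restate the power as about 76% to detect 72% versus 57%, giving the basis: 441 analysed, ICC 0.01, 12 degrees of freedom, equal cluster sizes.
- In the statistical analysis plan, if it does not already do so, fix a small-sample reference for the primary mixed-model test: between-within or similar degrees of freedom of about 11-12. Optionally, support it with a permutation test of service allocation within the hospital and non-hospital strata, which would be useful because the t reference itself drifted to 6.3-7.0% at ICC 0.05.

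The cost is a revised sentence, a line in the analysis plan, slightly wider intervals and a less favourable stated power. No extra participants are needed. The change makes the claim accurate; it does not restore 80%, which would take about 554 recruited across the same 14 services.

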### Statistical analysis

Generalised linear mixed models will be used to analyse the primary outcome of hospitalisation, and linear mixed models will be used for continuous outcomes. These will account for correlation between participants within a cluster. Analyses will be based on intention-to-treat and the level of significance will be set at p< 0.05.

### Economic evaluation

Economic evaluation will follow the protocol developed for our Phase II trial.^22 23^

*Cost comparisons*: Cost comparisons will include comparison of per person costs, including direct (health system) and indirect (personal) healthcare costs for the two groups. Direct costs will include staff time, consumables, communications and overheads. Intervention costs will include staff inputs by duration, type and resource use (including troubleshooting and support) and equipment. Personal costs will include transportation, travel time and impact of the intervention on the economic activities of other household members. Health system costs will include visits to the general practitioner, specialist or emergency department; use of chronic disease services; and hospitalisation.

*Cost-effectiveness analysis:* An incremental cost-effectiveness analysis will be undertaken to compare differences in costs between the two groups with differences in QALYs and number of hospitalisations in the 12-month follow-up period. For the former, a utility index will be calculated from the EQ-5D-5L by applying a ‘social tariff’, which then enables estimation of health benefits in terms of QALYs. The conversion to QALYs will be based on the assumption that for health states measured at successive points of time, the duration of each health state is exactly one half of the time interval between the two measurements.^47^ For the latter, the indicator of cost-effectiveness can be interpreted as the incremental cost of avoiding a hospitalisation.

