### Data collection and follow-up

Each participant will complete 8 weeks of rehabilitation and a follow-up of 12 months. Outcomes will be assessed at baseline, end of rehabilitation (after 8 weeks) and 12 months following the end of rehabilitation. We will undertake assessments with all participants (unless not possible, eg, due to death, loss-to follow-up, study withdrawal) at 8 weeks and 12 months irrespective of whether a participant has completed their pulmonary rehabilitation programme. Participants will record any healthcare utilisation during the 12 months follow-up (visits to health professionals, hospitalisations) in a diary. Each participant will be telephoned monthly during the 12 months by site research staff to encourage diary completion and capture patient-reported information on healthcare utilisation. These calls represent an additional contact with patients that would not be provided as part of routine clinical practice at trial sites, but the purpose of the call is only for research staff to support collection of data on healthcare use. Hospitalisation and use of other hospital services will be confirmed by medical record audit at 12 months, while 12-month medical and pharmaceutical resource use will be obtained from Services Australia using Pharmaceutical Benefits Scheme (PBS) and Medicare Benefits Schedule (MBS) data. Consent will be sought to use participants’ PBS and MBS data at the time of consent to the study. The schedule for assessments and follow-up is provided in table 1.

**Table 1 T1:** Schedule of trial follow-up and procedures

Assessment/procedure	Baseline	End rehabilitation programme	Monthly phone calls	12 months post rehabilitation programme
Informed consent	X			
Demographic information	X			
Programme completion		X		
6-minute walk test	X	X		X
Dyspnoea-12	X	X		X
Health related quality of life (EQ-5D-5L and CRQ)	X	X		X
Physical activity participation	X	X		X
Healthcare utilisation			X	X
Economic evaluation			X	X

CRQ, chronic respiratory questionnaire.

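### The economic evaluation charges the cost of the 8-week programme, but collects healthcare use and counts admissions only for the following 12 months, and it leaves the start of the QALY period unclear

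*Protocol article*

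**What the plan says.** **Timeline.** Data collection and follow-up puts the programme first and the follow-up second: "Each participant will complete 8 weeks of rehabilitation and a follow-up of 12 months".

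**Costs.** Economic evaluation counts programme delivery: "Intervention costs will include staff inputs by duration, type and resource use (including troubleshooting and support) and equipment". It also counts costs to the participant: "Personal costs will include transportation, travel time and impact of the intervention on the economic activities of other household members". Health system costs (GP, specialist, emergency department, chronic disease services, hospital) are added.

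**Effects.** The incremental analysis will "compare differences in costs between the two groups with differences in QALYs and number of hospitalisations in the 12-month follow-up period".

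**Collection of resource use.** The diary covers the period after rehabilitation: "Participants will record any healthcare utilisation during the 12 months follow-up". So do the calls: "Each participant will be telephoned monthly during the 12 months by site research staff to encourage diary completion". For national claims data, "12-month medical and pharmaceutical resource use will be obtained from Services Australia", with no start date given. Table 1 marks the healthcare utilisation and economic evaluation rows at the monthly calls and at 12 months, and leaves both blank at baseline and at the end of the programme.

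**Utility.** EQ-5D-5L follows the general schedule: "Outcomes will be assessed at baseline, end of rehabilitation (after 8 weeks) and 12 months following the end of rehabilitation". The QALY rule credits half of each interval to each of two successive measurements.

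**The concern.** A cost-effectiveness ratio is interpretable when costs and effects are accumulated over one stated period. Here the cost side reaches back into the programme for delivery and travel, while the stated collection of other healthcare use, and the count of admissions, starts only when the programme ends. The 8 weeks are also when the two service models differ most directly: participants travel to a centre or exercise at home.

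At stake is the second objective of the trial, the comparison of costs and cost-effectiveness. As written, the ratio would include what the programme costs in weeks 1-8 but not the GP visits, emergency attendances and admissions that occur alongside it. The analyst would also have to choose a QALY start point that the text does not settle.

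**Working it through.** The protocol states no economic result, so there is no figure to reproduce. The check compares the stated windows and then sizes the gap.

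**1. Windows side by side**

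| Component | Weeks 1-8 | Next 12 months | Source |
|---|---|---|---|
| Programme staff and equipment | counted | not applicable | Economic evaluation |
| Travel and household impact of the programme | counted; no collection mark in Table 1 | marked | Economic evaluation; Table 1 |
| Diary- and call-recorded healthcare use | not collected | collected | Data collection and follow-up; Table 1 |
| MBS/PBS claims | unclear | unclear (12 months, no start date) | Data collection and follow-up |
| Number of hospitalisations | not counted | counted | Economic evaluation |
| EQ-5D-5L | measured at both ends | measured at both ends | Table 1 |
| QALYs | unclear | counted | Economic evaluation |

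A 12-month claims extract cannot cover both the 8 weeks and the following 12 months, whichever start date is used.

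**2. Both readings of the QALY phrase**

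- If the 12-month qualifier governs QALYs, programme costs are charged but utility change in weeks 1-8 is left out.
- If it governs hospitalisations only, QALYs run over about 60 weeks while admissions and diary- and call-recorded use run over the last 52.

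Neither reading gives one window.

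**3. Share of the horizon**

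8 weeks = 56 days; 12 months = 365 days. 56/(56 + 365) = 56/421 = 13.3%.

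**4. QALYs at issue, if they start at the end of rehabilitation**

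Assume the arms are equal at baseline and differ in utility by d at week 8, and apply the protocol's half-interval rule.

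- Programme weeks: 0.5 × (56/365) × d = 0.077d.
- Following year, if a fraction e of d remains at 12 months: 0.5 × (1 + e) × d.

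| Fraction e remaining at 12 months | QALYs in follow-up year | Omitted share of total |
|---|---|---|
| 1 (held) | 1.00d | 0.077/1.077 = 7.1% |
| 0.5 (halved) | 0.75d | 0.077/0.827 = 9.3% |
| 0 (faded) | 0.50d | 0.077/0.577 = 13.3% |

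**5. Admissions in the programme weeks, for scale only**

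Sample size gives 57% and 72% free from admission at 12 months, so 43% and 28% admitted. Assume a constant hazard that also applies in the 8 weeks, and 490/2 = 245 participants per arm.

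- At 43%: rate = -ln(0.57) = 0.562 per year; 1 - exp(-0.562 × 56/365) = 8.3%, about 20 of 245.
- At 28%: rate = -ln(0.72) = 0.329 per year; 1 - exp(-0.329 × 56/365) = 4.9%, about 12 of 245.

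This shows the volume of first admissions that may fall outside the stated window. It does not estimate a between-arm difference during the programme, because the planning rates reflect the effect of completing it.

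**6. Planned travel**

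Control: 8 weeks × 2 sessions = 16 trips per participant. Choice arm at the expected 25% centre uptake: 0.25 × 16 = 4 on average. The planned contrast of 12 trips falls entirely in weeks 1-8. Attended trips will be fewer, since Sample size expects 49% completion for centre-based programmes.

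**The case against.** The case on the other side has real force.

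- **QALYs.** A reader might infer that QALYs are confined to the 12 months after rehabilitation. The documents do not establish that. The qualifier sits next to hospitalisations, the Abstract names changes in EQ-5D-5L as an input, EQ-5D-5L is measured at baseline and week 8, and the half-interval rule can start at baseline. This stands: the start point is unclear, not wrong.
- **No data from the programme.** A reader might infer that nothing economic is captured in weeks 1-8. That goes too far. EQ-5D-5L brackets the period, staff and equipment costs can come from site records, and travel can be approximated from sessions attended. The adverse event log covers hospitalisations over the trial period, although it is not named as an economic source. The stated gap is other healthcare use.
- **Deferred detail.** The section follows the Phase II economic protocol, which is not shown and may define a horizon. That would excuse silence. It does not remove the difference between windows that this article states, which would still have to be reconciled with its own Table 1.
- **Investment followed by benefit.** Setting programme costs against later outcomes is not wrong in itself. This stands. The difficulty is that other costs and admissions in the same weeks are left out.
- **Travel.** Personal costs are not confined to programme sessions and may include travel to later care. This stands, so travel costs arise largely, not wholly, in the programme.
- **Size.** The utility difference d is unknown and may be small, because the Introduction reports equivalent quality of life for home and centre delivery. The percentages are shares of a difference whose size is not known.

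**Conclusion.** The point holds as a mismatch between stated windows in the economic evaluation. Programme costs from weeks 1-8 enter the ratio. GP, specialist, emergency and hospital use in those weeks has no stated economic source, and admissions are counted only afterwards. Whether QALYs start at baseline or at the end of rehabilitation is left open.

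The uncovered period is 13.3% of the time from baseline. The 7% to 13% share of the QALY difference applies only if QALYs start after rehabilitation, and it rests on equal utility at baseline and straight-line change between measurements. The figure of about 12 to 20 first admissions per arm rests on a constant hazard.

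A reader might conclude that the ratio is biased or that the cost-effectiveness objective fails. The documents do not support that: neither the direction nor the net size of any effect on the ratio can be derived from them. This is a cheap improvement that makes the ratio coherent. It does not touch the definition or analysis of the primary outcome.

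**What to change.** 1. State one horizon for costs, QALYs and admissions in the economic evaluation: baseline to 12 months after rehabilitation.
2. State that QALYs are computed from the baseline, 8-week and 12-month EQ-5D-5L.
3. State the start date of the MBS/PBS extract and, where the consent allows, begin it at consent and run it to the end of follow-up.
4. In Table 1, mark healthcare utilisation and economic evaluation at the end-of-rehabilitation visit, so that service use, travel, time and household impact in weeks 1-8 are asked about there.
5. For participants already past week 8, use attendance records, the adverse event log and the hospital record audit, and say so.
6. Keep the ratio restricted to the 12 months after rehabilitation as a secondary result if wanted.

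The cost is a few questions at an existing visit, a longer claims extract and a wording change. The downsides are slight extra burden for participants and less complete programme-period data for those already enrolled; recruitment was still open at publication, so later participants can be captured prospectively. The article does not give the date range of the MBS/PBS consent, so that must be checked before the extract is lengthened.
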